### Study objectives

The primary objective of this study is to determine the feasibility of recruiting patients with acute stroke and TIA into an interventional randomised trial comparing the effect of different antihypertensive medication regimens on BPV.

Secondary feasibility objectives are:To determine the viability of measuring changes in BPV from baseline to 21 (±7) days and 90 (±14) days by treatment arm.To assess compliance rates with BPV measurement methods.To assess compliance rates with the investigational treatments.To identify serious adverse events (SAE) associated with the interventions, including recurrent stroke/TIA, other cardiovascular events, death and hospital readmission up to 3 months.

In addition to the feasibility objectives, exploratory outcomes that may be used in a future definitive RCT will be investigated. The proposed primary exploratory outcome will be modified Rankin Scale (mRS) score at day 90.

Exploratory secondary outcomes are:mRS at day 21.National Institutes of Health Stroke Scale (NIHSS) at day 21.Mean BP at day 21 and day 90.BPV at day 21 day and 90.Montreal Cognitive Assessment (MoCA) score at day 90.

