### Inclusion criteria

Age >18 years.Patients with first-ever clinically definite TIA and ischaemic stroke (NIHSS <10).Within 7 days of symptom onset (this criterion was initially within 72 hours of symptom onset, but was altered with a substantial amendment to the protocol to try and improve recruitment).Casual BP >130/80 mm Hg on repeat measurements.Ability to comply with randomly assigned BP-lowering regime and BP measurements.Able to understand written and verbal English.Able to give informed consent.Willing to allow his or her general practitioner (GP) and consultant, if appropriate, to be notified of participation in the study.

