### Exclusion criteria

The participant may not enter the trial if any of the following apply:Known definite contraindication to BP-lowering regime or therapeutic agents.Swallowing difficulties which would preclude the taking of oral medication.Definite indication for BB, CCB, ACEI or ARB therapy.Significant prestroke dependency (mRS >3).Coexisting life-threatening condition with life expectancy <3 months.Previous participation in this trial or current participation in another investigational drug trial.Atrial fibrillation.Female participants who are pregnant, lactating or planning pregnancy during the course of the study.Unable to understand written and verbal English.Cannot give informed consent.

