### Randomisation

After the baseline assessments eligible patients will be randomised using a computer-generated protocol, in blocks of 4, to a dihydropyridine CCB or ACEI/ARB-based regime. The study treatment will be dispensed at the baseline visit, but treatment will not be commenced within 48 hours of the qualifying event in keeping with current recommended practice. The actual therapeutic agent used will be at the discretion of the treating clinician, but dictated by the class of therapy that the participant is assigned to. Prescription of the medication will be done by the treating clinician and the initial supply will be dispensed by the treating hospital or community pharmacy in accordance with the hospital’s policy for providing discharge or outpatient medication. Further supplies will be provided by the participant’s GP. Unblinding will not be necessary as there is an open-label study design.

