### Interventions to be measured

#### Routine clinical data

The following routine clinical information and investigation results will be obtained from the medical notes and by participant interview:Demographics (including age, sex, ethnicity, height and weight, smoking and alcohol habits).Medical history and family history of cardiovascular disease.Concomitant medications.NIHSS.mRS (including premorbid mRS).Oxford Community Stroke Project and Trial of ORG 10172 in Acute Stroke Treatment classification.Laboratory tests (including full blood count, clotting, urea, electrolytes, creatinine, estimated glomerular filtration rate, total cholesterol and random glucose).12-lead ECG (±24 hours ECG if performed).Imaging investigations (including neuroimaging (CT or MRI), carotid ultrasound and cardiac echocardiography where applicable).

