#### Exploratory analyses

Mean BP will be calculated from enhanced casual measurements. Change in mean BP from baseline to follow-up by treatment arm will be compared using an independent samples t-test.

An assessment of treatment effect on BPV will be undertaken stratified according to treatment arm. A general linear model will be used with BPV as the dependent variable and treatment arm as the independent variable, adjusting for baseline BP and diagnosis (stroke vs TIA). Each expression of BPV as described above will be analysed.

Exploratory assessment of treatment effect on stroke outcome will be undertaken by comparing between-group differences in mRS and MoCA score at follow-up using independent samples t-tests or a non-parametric test if the assumptions of the t-test are violated.

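### Day-90 mRS, the lead exploratory outcome, is compared by an unadjusted t-test or unnamed rank test, with no ordinal effect measure and no use of diagnosis, NIHSS or premorbid mRS

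*Protocol article*

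**What the plan says.** - **Role of the outcome.** Study objectives states: "The proposed primary exploratory outcome will be modified Rankin Scale (mRS) score at day 90". Study overview adds the hope that the functional-outcome result will help in sizing a later definitive trial.
- **Analysis.** Exploratory analyses plans "comparing between-group differences in mRS and MoCA score at follow-up using independent samples t-tests or a non-parametric test". The second option applies when the first one's assumptions do not hold. The fallback test is not named, no criterion for the switch is given, and no effect estimate is attached to it.
- **Contrast within the same section.** The BPV model is fitted "adjusting for baseline BP and diagnosis (stroke vs TIA").
- **Population.** Eligible are "Patients with first-ever clinically definite TIA and ischaemic stroke (NIHSS <10"). The pre-stroke exclusion is "Significant prestroke dependency (mRS >3"), so premorbid scores up to 3 are admitted.
- **Baseline data.** Routine clinical data lists NIHSS and "mRS (including premorbid mRS"). Table 1 schedules both at baseline.
- **Allocation.** Patients are "randomised using a computer-generated protocol, in blocks of 4, to a dihydropyridine CCB or ACEI/ARB-based regime". No stratification by diagnosis is stated.

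**The concern.** The mRS is an ordinal scale from 0 to 6. In a mix of TIA and mild stroke, scores are likely to gather at the low end. A difference in means treats every step as equal, including the step to death. If the t-test assumptions are judged violated, which is foreseeable for a bounded, skewed score, the plan moves to a test that may deliver only a p-value. Sizing the next trial needs an estimate with an interval, on the scale that such a trial would use.

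Diagnosis, baseline NIHSS and premorbid mRS are also likely to explain much of the spread in day-90 mRS. A patient who enters with a premorbid score of 3 cannot be expected to finish at 0. The plan adjusts BPV for diagnosis but does not do so for functional outcome, where diagnosis probably matters more. A two-sample t-test or rank test leaves no place for covariates, so this is a feature of the stated method and not a detail left for later.

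**Working it through.** **1. The plan's own figure.** The Sample size calculation concerns systolic BPV, not mRS, but it supplies the 64 per arm used below.
- Pooled SD = sqrt((14.97² + 16.95²)/2) = 15.99.
- Normal approximation: n = 2(1.96 + 0.8416)² × 15.99²/8² = 62.7, so 63 per arm.
- Exact t-test: 63.7, so 64 per arm, with power 80.2%.
- Dropout: 128/0.85 = 150.6, so 151 against 150 stated.

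The figure reproduces. No power is claimed for mRS.

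**2. Chance imbalance in diagnosis.** Assume 40% TIA (not in the article) and simple 1:1 allocation. The SE of the between-arm difference in TIA share is sqrt(2 × 0.4 × 0.6/64) = 0.087, a 95% range of about ±17 points.

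**3. Power for mRS by simulation.** All inputs except the 64 per arm are assumptions:
- reference mRS 0–6 shares of 30/32/16/11/6/2/3%;
- 60% stroke and 40% TIA;
- a latent logistic model with one standardised severity score standing in for NIHSS and premorbid mRS;
- log-odds for diagnosis and per SD of severity of 0 and 0 (none), 1.0 and 0.8 (moderate), or 1.5 and 1.2 (strong);
- two-sided 5% level and 400 runs per scenario. The Monte Carlo SE of each rate is at most sqrt(0.5 × 0.5/400) = 2.5 points.

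Rejection rates in %:

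| Common OR | Covariates | t-test | Rank test | Unadjusted PO | Adjusted PO | Adjusted PO minus rank |
|---|---|---|---|---|---|---|
| 2.0 | none | 51.25 | 56.75 | 58.00 | 58.00 | 1.25 |
| 2.0 | moderate | 41.25 | 44.75 | 45.50 | 54.75 | 10.00 |
| 2.0 | strong | 32.50 | 38.00 | 38.00 | 57.00 | 19.00 |
| 1.5 | none | 20.25 | 21.75 | 22.00 | 20.25 | −1.50 |
| 1.5 | moderate | 13.75 | 17.50 | 17.75 | 22.50 | 5.00 |
| 1.5 | strong | 16.25 | 13.00 | 13.50 | 23.25 | 10.25 |

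(PO = proportional odds; the OR is conditional on the covariates.)

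With no effect (OR 1.0), rejection ranged from 4.0% to 5.75% across all methods and scenarios.

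**4. Reading the table.**
- The rank test and unadjusted PO agree within about 1 point, so the rank test itself loses almost nothing. The gain comes from adjustment.
- At OR 2.0 the t-test trails the rank test by 5.5, 3.5 and 5.5 points. At OR 1.5 the order is not consistent (−1.5, −3.75 and +3.25 points for the t-test), within simulation error.

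**The case against.** The strongest reply is that mRS is explicitly exploratory in a feasibility trial. The article powers only BPV and says no more than that it hopes to help with a future sample size. The suggested model would not give a decisive answer either: its power is only about 20–23% at OR 1.5 and 55–58% at OR 2.0. This stands, and it limits the weight of the point.

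Several stronger readings are tempting, and the article does not support them:

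- **No usable effect measure results.** The t-test route yields a mean difference and SDs that could size a trial on that scale, and nothing prevents tabulating mRS by arm. What the article lacks is a specified ordinal measure, and any estimate for the fallback. An analysis plan that is not shown may add one.
- **The tests are invalid, or imbalance biases them.** Randomisation makes the unadjusted comparison valid, and its standard error already covers chance imbalance. Imbalance of the size in step 2 costs precision. It does not create bias.
- **The data-dependent choice of test inflates error.** The rule is stated in advance, and each test alone holds its level. The two-stage choice was not simulated, so no harm is shown.
- **The loss is close to 20 points.** That is the top of a range that starts near 0. It requires strong covariate effects that the article does not quantify.

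One practical objection also stands. With the reference shares, 64 × 0.02 = 1.3 and 64 × 0.03 = 1.9 patients per arm would sit at scores 5 and 6, so proportional odds can be checked only roughly.

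**Conclusion.** The point holds as an improvement to a valid but blunt exploratory analysis. The article commits its lead exploratory outcome to an unadjusted t-test or unnamed non-parametric test, sets no ordinal effect measure, and leaves three recorded, likely prognostic variables out.

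The size of the loss rests on the assumed mRS shares, diagnosis mix and covariate strengths. If the covariates were not prognostic, adjustment would gain essentially nothing. Whatever their strength, a specified estimate with an interval would still serve the stated aim of informing a definitive trial better than a possible bare p-value. The importance is minor to moderate. The recruitment and retention objective, the safety comparison and the stated sample size are not affected.

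**What to change.** Replace the t-test/non-parametric rule for mRS with wording such as:

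> mRS at day 90 and at day 21 will be analysed over its full range (death = 6) by proportional-odds logistic regression on treatment arm, adjusted for diagnosis (stroke or TIA), baseline NIHSS and premorbid mRS. The common odds ratio with 95% CI and the mRS distribution by arm will be reported. Sparse top categories will be merged if needed, by a rule set before arm-level data are examined. A rank test will be a sensitivity analysis.

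The adjusted odds ratio is conditional on these covariates. Anyone using it to size the definitive trial should assume the same adjustment there.

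The cost is a change of wording, with no new data, visits or patients. The article reports recruitment as ongoing, so at that stage the change could be specified before analysis. The downside is reliance on the proportional-odds assumption, which can be checked only roughly at this size. The tabulated distributions and the rank test give some protection.

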### Ethics and dissemination

This study was granted ethical approval in England (London–Central Research Ethics Committee, REC 17/LO/1427) and clinical trial authorisation from the Medicines and Healthcare products Regulatory Agency (EudraCT number 2017-002560-41). Subsequently, the trial was approved by the Health Research Authority. Study oversight will be conducted through regular meetings of a Trial Steering Committee and a separate Safety Committee, both of which will include independent representatives. If it is felt that the risk to participants is significant or unacceptable the Safety Committee can recommend early termination of the trial.

The proposed investigational medicinal products are antihypertensives that are already in routine use and so their safety profiles are known. The medications are expected to lower the BP of participants. Therefore, in line with accepted stroke guidelines we will only recruit patients with uncontrolled BP (>130/80 mm Hg) who would otherwise require antihypertensive treatment for secondary stroke prevention. Medications that inhibit the renin-angiotensin system are known to potentially cause kidney dysfunction in patients with unrecognised renal artery stenosis. To ensure the safety of patients commenced on these medications a blood test for kidney function will be done at the 2–4 weeks follow-up which is in keeping with standard practice.

The trial will be conducted in accordance with the Declaration of Helsinki and the ICH Guidelines for Good Clinical Practice. All participants will provide written informed consent. Data will be collected and handled in line with sponsor standard operating procedures and NHS Trust policies. Electronic data will be anonymised and all data will be kept under secure conditions. [name] will act as data custodian.

Dissemination of the study results is planned via publication in peer-reviewed medical journals and presentation at relevant scientific conferences. Any reporting will adhere to the Consolidated Standards of Reporting Trials statement extension for pilot and feasibility trials. We do not intend to employ professional writers.
